##### Face-Name Paired Associates Task

The paired associates task will assess encoding and retrieval processes. The task consists of 10, 30-s encode blocks alternating with recall blocks, with each block separated by a resting baseline block. In the encoding blocks, participants are shown pictures of faces paired with audio recordings of names and asked to indicate if they feel the name fits the displayed face. This ensures that participants are attending to the stimuli and processing the face-name pairing, allowing them to carry out the recall task. In the recall blocks, participants are shown the same faces paired with audio recordings of names. Half of the names would have been previously paired with the same face, while the other half would not. Participants indicate if the face-name pairings were the same as before.

##### Singing Task

Participants listen to five short tunes and hum each melody after hearing it. The familiar melodies are taken from the repertoire of the choral intervention.

##### Melodic Memory Task

The task involves musical encoding and recall. In the encoding phase, participants are instructed to listen carefully to 20 short (4–6 s) newly-composed melodies. Stimuli will be presented in a block design, with five blocks of four melodies each, separated by resting baseline blocks. In the recall phase (taking place outside the scanner), participants hear 40 melodies and indicate which melodies were heard in the encoding phase. They are also asked to rate, on a scale of 1–7, how much they liked each melody, for the assessment of implicit memory.

These fMRI tasks were designed to involve the sense of hearing. Unfortunately, both memory functions and the auditory cortex are located in the temporal lobe. An auditory localizer scan allows exclusion of the auditory cortex when performing memory-related analyses.

#### Frequency of Assessments

Follow-up assessments will be conducted 6 months after the start of the intervention, at the end of the first year and at the end of the second year. Details of all measurements at baseline and each follow-up visit are listed in Table 2.

## Methods of Analysis

CCTS at each follow-up visit, absolute changes from baseline and percentage changes from baseline during the intervention period will be compared between the two arms using Student’s *t*-test and repeated-measures analysis of variance (ANOVA). Following this, a linear mixed-effects model will be conducted to examine the main effect of time and group allocation, and the interaction between time and group allocation, adjusting for potential confounders where necessary. Fisher’s exact tests will be used to compare the difference in dichotomous outcome measures such as cognitive decline, defined as the one or more points in MMSE score, between the two arms. Multiple logistic regressions with adjustment for important baseline characteristics will be conducted in the event of important baseline non-comparability. Statistical analysis will be conducted using SPSS, Stata or R. Interim analysis will be conducted for the first group of participants using data collected at 6 months, 12 months and 24 months, respectively.

The statistical analysis for DNA methylation will be performed using a modified version of the CPACOR pipeline to eliminate potential confounders such as bisulfite conversion, batch effect, and white blood cell composition (Lehne et al., 2015). Marker intensities will be normalized by quantile normalization. We will use the epigenome-wide methylation scores to impute white blood cell subsets using the Houseman method (Houseman et al., 2014). A principal components analysis will also be performed to quantify latent structure in the data, including batch effects. Single-marker tests using logistic regression will be used to examine the association of each autosomal CpG site with condition (choral singing/control), adjusted for age and sex. We will also calculate the methylation age using the 353 CpG sites previously identified (Horvath, 2013). Principal components from intensity values of Infinium control probes, which accounts for various technical parameters such as bisulfite conversion batch, will also be included as covariates in the regression models. Finally, the association results will be adjusted for genomic control inflation factor.

MRI images obtained from baseline and follow-up visits will be used to track relevant features such as hippocampal, whole-brain, total cerebral volume and annualized rate of atrophy; total ventricular volume, temporal horn volume; white matter volume and shape; fractional anisotropy and mean diffusivity and radial diffusivity; and the number of white matter lesions and cerebral micro-bleeds. Software such as FreeSurfer and BrainVoyager will be used in image processing and analysis. Functional connectivity analysis will be conducted using group ICA to track changes in networks such as the default mode network and the social brain network. As the face-name paired associates and melodic memory tasks are expected to involve episodic memory, the hippocampus is an *a priori* area of interest. Hemodynamic response function (HRF) time-locked to the presentation of stimuli will be extracted and analyzed.

For all data sets, a linear mixed-effects model will be used to analyze changes in mean responses over time for each group and the interaction term between group allocation and the time variable. A significant group × time interaction will indicate an effect of the choral singing intervention, following which appropriate *post hoc* tests can be done.

Intention-to-treat and per protocol analyses will be conducted. Compliance is monitored. Sensitivity analysis will be conducted by excluding subjects whose compliance (attendance) rate is below a specific cutoff point.

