## Materials and Methods

### Participants

Trial participants are community-living elderly aged 60 years and above. Some are participants from two previous studies on healthy aging (approval number: NUS 1351 and NUS 2501) who had consented to be contacted for future research, with additional participants recruited through door-to-door visits. Screening is done by trained research nurses and psychologists. Participants are included if they presented self-reported subjective cognitive complaints, objective cognitive impairment based on neuropsychological test scores (age- and education-standardized Z-scores in the range of 0 to −1.5 for at least five tests, out of 10) or at least two risk factors of dementia (family history of dementia, physical inactivity, low social engagement, heart disease, transient ischemia attack, diabetes, head injury, living alone and depressive symptoms), but are not demented (Clinical Dementia Rating global score = 0). Exclusion criteria are conditions preventing effective engagement in the intervention, such as: terminal illness, stroke, aphasia and marked hearing impairment, as well as participation in another interventional study.

Eligible participants are given sufficient information about the study and provide their informed consent prior to a screening assessment. Results of the screening also act as a baseline measurement. Recruitment will proceed until a total of 360 participants is reached.

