#### Cognitive and Psychological Measures

The *primary outcome* of the study is change in cognitive performance as measured with a CCTS based on results from a neuropsychological test battery. The CCTS is the average of Z-scores standardized to the baseline mean and standard deviation of the trial participants, with higher scores representing better cognitive performance. The test battery evaluates cognitive function in specific cognitive domains such as verbal memory (Rey Auditory Verbal Learning Test; Rey, 1964), attention (Digit Span (WAIS-III UK); Wechsler, 1997), executive function (Color Trails Test 1&2; D’Elia et al., 1996), visuospatial functioning (Block Design (WAIS-III UK); Wechsler, 1997), information processing speed (Symbol-Digits Modalities Test; Smith, 2013) and language (Boston Naming Test; Kaplan et al., 1983). Trained research staff administer the tests in the participant’s most proficient language. The effects of language and culture are minimized by using test items familiar to the study population.

*Secondary cognitive outcomes* include cognition measured by a modified version of the Mini-Mental State Examination (MMSE; Folstein et al., 1975; Feng et al., 2012), the Montreal Cognitive Assessment (MoCA; Nasreddine et al., 2005) and scores from each of the above neuropsychological tests. Individual test scores are standardized (z-transformed) using normative data of the local population (see Supplementary Tables S1, S2).

Other secondary outcomes measured are severity of dementia symptoms (Clinical Dementia Rating scale; Morris, 1993); neuropsychiatric symptoms (Neuropsychiatric Inventory; Cummings et al., 1994); depressive symptoms (Geriatric Depression Scale; Yesavage and Sheikh, 1986); anxiety symptoms (Geriatric Anxiety Inventory (GAI); Pachana et al., 2007); perceived stress (Perceived Stress Scale (PSS); Cohen et al., 1983); and sleep quality (Pittsburgh Sleep Quality Index (PSQI); Buysse et al., 1989).

We also collect data on musical skill and engagement (Goldsmiths Musical Sophistication Index; Müllensiefen et al., 2014), social cognition and rhythmic entrainment but these measures will not be used as trial outcomes for primary analysis.

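### Percentage change from baseline is not interpretable for the CCTS, whose baseline mean is zero by construction; that one listed comparison of the primary outcome should be deleted

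*Protocol article*

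**What the plan says.** The protocol article, under Cognitive and Psychological Measures, defines the primary outcome as "change in cognitive performance as measured with a CCTS based on results from a neuropsychological test battery". It constructs the score as follows: "The CCTS is the average of Z-scores standardized to the baseline mean and standard deviation of the trial participants". A higher score is better.

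Methods of Analysis then lists what will be tested between arms by Student's t-test and repeated-measures ANOVA: the CCTS at every follow-up, and also "absolute changes from baseline and percentage changes from baseline during the intervention period". The three forms (visit score, absolute change, percentage change) stand side by side without ranking. After these comparisons, "a linear mixed-effects model will be conducted to examine the main effect of time and group allocation" and their interaction. The same section later applies a mixed model to all data sets and takes a significant group × time interaction as the sign of an intervention effect.

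Nothing in the article moves the CCTS to a positive scale. The standardization to local normative data concerns the individual test scores, which are secondary outcomes.

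**The concern.** A percentage change needs a scale with a true zero and positive values. On the CCTS, zero means only the average trial participant at baseline. Dividing by a baseline that straddles zero does three things:

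- it reverses the sign for everyone who starts below average;
- it gives enormous values to anyone who starts close to average;
- it has no value at exactly zero.

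Software returns a number for every non-zero baseline without warning, so the fault would not show itself in the output. The result would be reported next to valid comparisons of the primary outcome. It could seem to contradict a real benefit or, by chance, show a large effect in either direction. The planned interim analyses of the first group at 6, 12 and 24 months mean that the wording could be applied before the final analysis.

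**Working it through.** The article gives no SD, effect size, alpha or power for the CCTS, so there is no stated figure to reproduce. Steps 1 and 2 need only the article's own definition. Steps 3 to 5 show the size of the problem under stated assumptions.

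**Step 1: baseline mean.** Each test's Z-score is (x − baseline mean)/baseline SD, which averages 0 over the standardizing sample. The average of several such scores also averages 0. With a roughly symmetric distribution, about 50% of participants have a negative baseline.

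**Step 2: the ratio.** Percentage change = 100 × (Y1 − Y0)/Y0.

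| Baseline | Follow-up | Absolute change | Percentage change |
|---|---|---|---|
| 0.50 | 0.75 | +0.25 | +50% |
| -0.50 | -0.25 | +0.25 | -50% |
| -0.50 | -0.75 | -0.25 | +50% |
| 0.02 | 0.27 | +0.25 | +1250% |
| -0.02 | 0.23 | +0.25 | -1250% |

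The same gain of 0.25 gives four different percentages, two of them negative, and a decline is recorded as +50%.

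**Step 3: inputs for the size.** From the article: "Recruitment will proceed until a total of 360 participants is reached", allocated 1:1, so 180 per arm. Assumed: normal scores, CCTS SD 0.65, baseline to follow-up correlation r of 0.6 to 0.8, true benefit d = 0.15 CCTS units, two-sided 5% test.

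**Step 4: spread of the percentage.**

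- Share with a baseline within 0.1 of zero: 2Φ(0.1/0.65) − 1 = 0.122, about 12%.
- With no effect, write Y1 = r·Y0 + e. Then percentage change = 100 × [(r − 1) + e/Y0], and e/Y0 is √(1 − r²) times a standard Cauchy variable, which has no finite mean or variance. Its 1st and 99th percentiles are ∓tan(0.49π) = ∓31.82.
- r = 0.6: 100 × (−0.4 ∓ 0.8 × 31.82), or −2,586% to +2,506%.
- r = 0.7: 100 × (−0.3 ∓ 0.714 × 31.82), or −2,302% to +2,242%.
- r = 0.8: 100 × (−0.2 ∓ 0.6 × 31.82), or −1,929% to +1,889%.

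The range is therefore roughly ±1,900% to ±2,600%, depending on r. It is somewhat wider once a benefit is added.

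**Step 5: power.** Absolute change has SD = 0.65 × √(2(1 − r)), SE = SD × √(2/180), and power ≈ Φ(0.15/SE − 1.96).

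| r | SD of change | SE | 0.15/SE | Power, absolute change |
|---|---|---|---|---|
| 0.6 | 0.581 | 0.0613 | 2.45 | 69% |
| 0.7 | 0.503 | 0.0531 | 2.83 | 81% |
| 0.8 | 0.411 | 0.0433 | 3.46 | 93% |

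For percentage change, a uniform benefit d adds 100·d/Y0 to each treated participant. Because Y0 is symmetric about 0, these additions are as often negative as positive, and the benefit does not accumulate. Simulation at the same settings gives about 2% power, with the arm difference pointing the wrong way in about half of runs.

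A second set of assumptions gives the same picture: six component scores, inter-test correlation 0.3 to 0.5 (CCTS SD 0.65 to 0.76), r of 0.70 to 0.85, benefit 0.2 SD. The percentage-change test rejects in 1.5% to 2.1% of runs with a true benefit and 1.8% to 2.4% without one.

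**The case against.** The strongest reply is that the plan does not depend on this comparison. Absolute change satisfies the definition of the primary outcome, and Methods of Analysis names the group × time interaction in a mixed model as the evidence of an effect. That stands, and it limits the seriousness of the point.

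Several stronger readings are tempting, and the document does not support them:

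- *The primary result is invalid.* It is not. CCTS at each visit, absolute change and the mixed model never divide by the baseline.
- *Every participant's percentage is wrong.* The sign is reversed only for negative baselines, and the value is undefined only at exactly zero. A positive baseline keeps the correct sign, though the value is still unstable near zero.
- *False positives are inflated.* In simulation with no effect the test rejects in 1.8% to 2.4% of runs, below the nominal 5%. The harm is an uninformative result of arbitrary direction.
- *Other Z-scored outcomes share the fault.* The sentence assigns percentage change to the CCTS alone.
- *A baseline-adjusted model is needed.* That is a separate choice, and curing this defect does not require it.

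A further reply is that a statistical analysis plan, not shown here, may settle the matter. That would answer an omission. Here the article states a specific quantity for a fully defined score, and the two statements do not fit together.

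**Conclusion.** The point holds for one listed comparison of the primary outcome. The sign reversal below zero and the instability near zero follow from the article's own definition of the CCTS, whatever the SD or correlation. That about half of participants start below zero assumes rough symmetry. The loss of power to about 2%, against about 69% to 93% for absolute change, rests on the assumed normal scores, SD 0.65, correlation 0.6 to 0.8, benefit 0.15 and 180 analysed per arm; it illustrates the size and is not a figure of this trial. Because the remaining analyses of the CCTS are sound, this should be corrected before analysis but does not threaten the trial's main conclusion.

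**What to change.** In Methods of Analysis, delete percentage change from baseline for the CCTS. Report the between-arm difference in CCTS units (the baseline-standardized scale) with a 95% CI, taken from the absolute-change comparison or the mixed model that the plan already contains. The cost is one line of wording, with no change to participants, visits, data collection or sample size.

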### Randomization

Following informed consent, randomization into intervention or control arm is performed with a 1:1 allocation ratio. Balanced treatment assignments will be achieved using permuted block randomization. The block length is determined by an independent statistician and is not made known to the clinical investigators or site personnel. Opaque, sequentially numbered and sealed envelopes are prepared for the randomization process. Authorized site personnel open the randomization envelopes in sequential order to determine the participant’s treatment arm and the identification number to be used for that participant.

Participants randomized to the intervention arm participate in choral singing for 2 years while participants in the control arm take part in general health education and group activities.

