**Figure 2 F2:**
[figure not shown]
Flow diagram of participants’ progression through phases of RCT as of May 2017. Adapted from Schulz et al. (2010). *Other reasons: four with hearing impairment, one with visual impairment, one with advanced cancer, two participating in other studies, two received recent neuropsychological assessment, one relocated outside the defined recruitment area.

**Table 3 T3:** Baseline characteristics of the first 93 randomized trial participants.

Variable	Choral singing (*n* = 47)	Controls (*n* = 46)	*p*-value
Age (year), mean (SD)	70.98 (0.835)	69.39 (0.779)	0.168
Women, n (%)	76.6	80.4	0.652
Education, n (%)			0.235
No formal schooling	21.3	8.7	
Primary and below	53.2	63.1	
Secondary and above	25.5	28.2	
Marital status			0.925
Married	55.3	54.3	
Divorced/Widowed/Single	44.7	45.7	
Living alone, n (%)	14.9	15.2	0.965
SMCC total score, mean (SD)	39.32 (0.964)	38.41 (0.642)	0.438
MMSE total score, median (IQR)	29 (27–30)	29 (27–30)	0.720
MoCA total score, median (IQR)	26 (24–28)	26 (25–29)	0.766
GDS total score, median (IQR)	2 (0–3)	1 (0–2.25)	0.246
GAI total score, median (IQR)	0 (0–4)	0 (0–1)	0.122
PSS total score, mean (SD)	15.53 (0.633)	14.91 (0.493)	0.444
GoldMSI score, mean (SD)	58.94 (1.71)	55.93 (1.79)	0.229

*Baseline comparability of the randomized groups was assessed using independent samples Student’s t-tests for continuous variables meeting the assumption of normality and Mann-Whitney tests for variables violating the normal distribution assumption. Chi-square tests and Fisher’s exact test were run for dichotomous variables. No significant differences between randomized groups were found*.

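### Binary cognitive decline is set at one MMSE point with no direction, visit or error margin, so a material share of stable participants would count as decliners

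*Protocol article*

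**What the plan says.** All references are to the protocol article.

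- **Methods of Analysis:** "Fisher’s exact tests will be used to compare the difference in dichotomous outcome measures". The example given is "cognitive decline, defined as the one or more points in MMSE score, between the two arms". The sentence does not say whether the points are lost or gained, from which visit to which, or whether the change must be confirmed. Adjusted logistic regression is planned only if important baseline imbalance appears.
- **Cognitive and Psychological Measures:** the MMSE is a secondary outcome, in "a modified version of the Mini-Mental State Examination". The primary outcome is change in the composite cognitive test score (CCTS).
- **Table 1:** the MMSE is taken at baseline, 6 months, 1 year and 2 years.
- **Progress, Table 3:** baseline MMSE is median 29 (IQR 27–30) in both arms, for the first 93 participants.
- **Methods of Analysis, closing paragraphs:** a linear mixed model with a group-by-time term is planned for every data set.

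No MMSE retest error, reliability or expected decline rate is given anywhere.

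**The concern.** A cut at the smallest recordable change leaves no room for measurement error. An upper quartile of 30 means that at least a quarter of participants start at the top of the scale (if its maximum is 30). They cannot score higher, so error at follow-up can only leave them there or move them down. Some people whose cognition has not changed will therefore be counted as decliners in both arms.

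If the error is the same in both arms, the reported decline rate is too high and the difference between arms shrinks. This is the only definition of a decline event that the article gives, so a reader will look to it for a plain statement of how many people declined.

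The missing direction and visit matter separately. A fall at any follow-up visit and a fall at 2 years are different outcomes with different rates, and the text allows either.

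**Working it through.** The plan states no decline rate, retest error or power for this outcome, so there is no figure to reproduce. The check below rests on stated assumptions.

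**Inputs from the article.** Baseline quartiles are 27/29/30 (Table 3). On numbers, "Recruitment will proceed until a total of 360 participants is reached" (Participants) and "randomization into intervention or control arm is performed with a 1:1 allocation ratio" (Randomization), which gives 360/2 = 180 per arm.

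**Assumptions.** Scale maximum 30; per-occasion error SD 0.3 to 1.5 points; 10–40% truly declining, by 1 to 3 points; two-sided alpha 0.05; no dropout; the rule read as a fall from baseline.

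**Model.** True score is Normal with mean 28.7. Normal error is added so that the total SD is 2.2, and the result is rounded and capped at 30. At every error SD tried this returns quartiles 27/29/30. Follow-up is an independent remeasurement.

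**Step 1: stable participants counted as decliners (FP)**

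| Error SD | 0.3 | 0.5 | 0.75 | 1.0 | 1.25 | 1.5 |
|---|---|---|---|---|---|---|
| Fall of at least 1 | 12% | 19% | 24% | 28% | 31% | 34% |
| Fall of at least 2 | 0.1% | 1.6% | 5.6% | 10.1% | 14.2% | 17.6% |
| Fall of at least 3 | 0% | 0% | 0.6% | 2.4% | 4.9% | 7.5% |

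The first row is for one visit. If the rule means a fall at any of the three follow-up visits, it becomes 23–59% (50% at error SD 1.0).

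**Step 2: share of counted decliners that is false.** With π the true decline rate and Se the chance that a true decliner is counted, the share is (1−π)FP / [(1−π)FP + πSe]. For a true 2-point drop at error SD 1.0, FP = 0.281 and Se = 0.78:

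- π = 10%: 0.2529/(0.2529 + 0.078) = 76%
- π = 20%: 0.2248/(0.2248 + 0.156) = 59%
- π = 30%: 0.1967/(0.1967 + 0.234) = 46%
- π = 40%: 0.1686/(0.1686 + 0.312) = 35%

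Over all error SDs and drops tried, the share runs from 16% to 85%. It exceeds half in every scenario at π = 10%. At 30% it does so only with small true drops and larger error.

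**Step 3: dilution.** True rates are 20% (control) v 10% (choir), and the observed rate is πSe + (1−π)FP. For error SD 0.5 and a 2-point drop (FP = 0.188, Se = 0.88):

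- control: 0.2×0.88 + 0.8×0.188 = 0.326
- choir: 0.1×0.88 + 0.9×0.188 = 0.257

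| Error SD | True drop | Observed rates | Power, normal approx. (simulated Fisher) |
|---|---|---|---|
| perfect classification | – | 20% v 10% | 0.76 (0.73) |
| 0.5 | 2 | 33% v 26% | 0.30 (0.26) |
| 0.5 | 3 | 34% v 26–27% | 0.35 (0.32) |
| 1.0 | 2 | 38% v 33% | 0.17 (0.15) |
| 1.0 | 3 | 41% v 34–35% | 0.24 (0.22) |

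Power fell in every scenario tried.

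**Step 4: would a stricter cut help?** Normal-approximation power at cuts of at least 1, 2 and 3 points:

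| Error SD | True drop | ≥1 | ≥2 | ≥3 |
|---|---|---|---|---|
| 0.5 | 2 | 0.30 | 0.45 | 0.19 |
| 0.5 | 3 | 0.35 | 0.64 | 0.52 |
| 1.0 | 2 | 0.17 | 0.20 | 0.17 |
| 1.0 | 3 | 0.24 | 0.36 | 0.37 |

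Simulated Fisher tests for the first row give 0.26, 0.37 and 0.10, in the same order. A 3-point cut can therefore do worse than the 1-point cut.

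**Step 5: where a reliable-change limit would fall.** The limit is 1.645 × SD of the difference in stable participants:

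- error SD 0.3: 1.645×0.50 = 0.82, so 1 point
- error SD 0.5: 1.645×0.69 = 1.14, so 2 points
- error SD 1.0: 1.645×1.21 = 1.99, so 2 points, only just
- error SD 1.5: 1.645×1.73 = 2.85, so 3 points

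Of these four, one point passes only at error SD 0.3. Because scores are whole numbers, the false rate at these limits is not exactly 5% (12%, 1.6%, 10.1% and 7.5% from Step 1).

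**The case against.** The strongest reply is that little rests on this outcome. The trial is judged on the CCTS, chosen as more sensitive to early change. The MMSE is secondary, and its binary version is only an example of a dichotomous measure. Follow-up assessors are blind to allocation, so misclassification should be alike in both arms: it costs power but does not create false positives. The mixed model for all data sets, read as including the MMSE, already analyses the score without a cut. All of this stands and limits the point to one secondary outcome.

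Two stronger readings are tempting, and the documents support neither.

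- A reader might infer that one point lies within retest noise and that most counted decliners would be false. Both need a retest error and a true decline rate that are not given. The second holds near 10% true decline, is borderline near 20% and mostly fails at 30% or more. The baseline also comes from 93 of a planned 360 participants, on a modified instrument.
- A reader might infer that a 3-point cut is the remedy. Step 4 shows that it can lose power when true drops are 2 points.

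The reply does not rescue the rule itself. It is stated, not left to a fuller document, and it is incomplete as printed. No justification against measurement error is offered.

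**Conclusion.** The point holds for the secondary binary outcome. As written, the rule would label about 12–34% of truly stable participants as decliners at one visit, for an assumed error SD of 0.3 to 1.5. That inflates the decline rate and weakens the Fisher comparison: an assumed true contrast of 10 percentage points shrinks to roughly 5 to 8 at error SD 0.5–1.0. These sizes depend on the assumed error, decline rate and drop. The direction does not, provided that error is alike in both arms. The missing direction and visit are certain from the text. The randomised comparison remains valid, with no inflation of type I error and no effect on the CCTS analysis.

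**What to change.** Before the final unblinded comparison:

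1. Define decline as a fall from baseline to a named visit (2 years) that exceeds 1.645 × the standard error of the difference, estimated from this modified MMSE's own data pooled over arms. Change between visits includes some real change, so this estimate errs on the strict side; report the false rate that the whole-number cut implies. Alternatively, require a fall confirmed at the next visit. With the last assessment at 2 years, only falls first seen at 6 months or 1 year can be confirmed.
2. Do not fix a 3-point cut in advance.
3. Analyse the outcome by logistic regression adjusted for baseline MMSE in all cases, not only when imbalance appears.
4. State that the continuous mixed model already planned is the main MMSE analysis.

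First-group data at 6 months and 1 year are already in hand and interim analyses are planned. The limit should therefore be set without reference to arm, and the change dated.

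**Cost:** a change of definition, with no new data if the error can be estimated from existing visits. There will be fewer counted events. If true drops are only 1–2 points there may be little or no gain in power, and a strict limit could lose some.

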### Assessments and Outcome Measures

A comprehensive assessment protocol with cognitive and psychological measures, blood and urine biomarkers and brain MRI measures has been designed for this study. Participants undergo questionnaire-based interviews, cognitive testing, clinical assessments, specimen collection and MRI prior to, during and at the end of the intervention (Table 1). Assessors at each follow-up are blind to group allocation.

**Table 1 T1:** Measurements and visit schedules.

	Measurement	Baseline	6 months	1 year	2 year
1	Social, demographic and lifestyle data	√			
2	Medical conditions and medications	√			
3	Mini mental state examination (MMSE)	√	√	√	√
4	Subjective memory and cognitive complaint	√		√	√
5	Neuropsychological testing/assessment	√		√	√
6	Clinical dementia rating (CDR)	√		√	√
7	Neuropsychiatric inventory (NPI)	√		√	√
8	Activities of daily living (ADL)	√		√	√
9	Instrumental activities of daily living (IADL)	√		√	√
10	Pittsburgh sleep quality index (PSQI)	√	√	√	√
11	Geriatric depression scale (GDS-15)	√	√	√	√
12	Geriatric anxiety inventory (GAI)	√	√	√	√
13	Perceived stress scale (PSS)	√	√	√	√
14	Rhythm experiment	√		√	√
15	The social cognition and behavior assessment	√		√	√
16	Gold-MSI	√			√
17	Venous blood sample collection	√		√	√
18	Urine sample collection	√	√	√	√
19	Brain MRI, blood pressures, pulse rates	√		√	√

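### Covariates enter only on undefined need or observed imbalance, and no stated CCTS analysis conditions on baseline CCTS, which costs some power and leaves analyst discretion

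*Protocol article*

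**What the plan says.** The primary outcome "is change in cognitive performance as measured with a CCTS based on results from a neuropsychological test battery" (Cognitive and Psychological Measures). In Table 1 the row "Neuropsychological testing/assessment" is ticked at baseline, 1 year and 2 years.

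Methods of Analysis treats CCTS in two steps. First, t-tests and repeated-measures ANOVA compare the arms on the score at each follow-up visit, on absolute change and on percentage change. No covariate is mentioned. Second, a linear mixed model has time, group and their interaction, "adjusting for potential confounders where necessary". The same section later applies this model to all data sets and takes a significant interaction as the sign of an effect.

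Dichotomous outcomes, such as decline defined on the MMSE, are compared by Fisher's exact test. Then: "Multiple logistic regressions with adjustment for important baseline characteristics will be conducted in the event of important baseline non-comparability".

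The Randomization section says "randomization into intervention or control arm is performed with a 1:1 allocation ratio" and "Balanced treatment assignments will be achieved using permuted block randomization"; it names no stratification factor. The footnote to Table 3, on the first 93 participants, reports baseline tests and says "No significant differences between randomized groups were found".

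**The concern.** Two features of the stated plan are weak.

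**The trigger for covariates.** In a properly randomized trial any baseline difference between arms is due to chance. The reason to adjust is that a variable predicts the outcome, and that is known before the data are seen. Under the stated rules, whether covariates enter depends on a later judgement of need or of important imbalance, and neither is defined. The fitted model can then vary with the data and with the analyst.

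**The use of baseline CCTS.** If the mixed model takes baseline as one visit category, gives group a free effect there and has complete data, its interaction at 2 years is the difference between arms in raw change. So neither the change-score t-test nor the model conditions on baseline CCTS. The visit-wise t-tests leave it out altogether.

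The documents themselves point to likely prognostic variables. Eligibility uses test scores standardized for age and education, whereas the CCTS is standardized only to the trial's own baseline mean and SD, so age and education differences remain in it. For the methylation tests the article does fix age and sex as covariates. It does not do so for the primary outcome.

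**Working it through.** **Inputs from the documents.** Total sample: "Recruitment will proceed until a total of 360 participants is reached". With 1:1 allocation this is 360/2 = 180 per arm. The article states no power, alpha, SD, effect size or correlation, so there is no figure of its own to reproduce.

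**Assumptions.** Equal variance at baseline and follow-up; baseline-to-follow-up correlation r from 0.5 to 0.9; two-sided alpha 0.05; no dropout. For power: a difference of 0.15 CCTS units with SD 0.65 (0.15/0.65 = 0.23 SD), and as a second case 0.25 SD.

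**Step 1: relative variance of the treatment contrast.** Follow-up score only: 1. Change score: 2(1-r). Baseline-adjusted: 1-r². Hence adjusted/change = (1-r²)/[2(1-r)] = (1+r)/2, a saving of (1-r)/2. Against follow-up only, the saving is r².

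| r | Follow-up | Change | Adjusted | Saving vs change | Saving vs follow-up |
|---|---|---|---|---|---|
| 0.5 | 1 | 1.00 | 0.75 | 25% | 25% |
| 0.6 | 1 | 0.80 | 0.64 | 20% | 36% |
| 0.7 | 1 | 0.60 | 0.51 | 15% | 49% |
| 0.8 | 1 | 0.40 | 0.36 | 10% | 64% |
| 0.9 | 1 | 0.20 | 0.19 | 5% | 81% |

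**Step 2: power.** Power = Φ(difference/SE - 1.96), with SE = SD × √(2 × relative variance/180). For r = 0.7 and the change score, SE = 0.65 × √(2 × 0.60/180) = 0.0531, 0.15/0.0531 = 2.83, and power is 81%. With adjustment, SE = 0.65 × √(2 × 0.51/180) = 0.0489, 0.15/0.0489 = 3.07, and power is 87%.

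| r | 0.15 units, SD 0.65: follow-up / change / adjusted | 0.25 SD: follow-up / change / adjusted |
|---|---|---|
| 0.6 | 59 / 69 / 78% | 66 / 76 / 84% |
| 0.7 | 59 / 81 / 87% | 66 / 87 / 91% |
| 0.8 | 59 / 93 / 95% | 66 / 96 / 98% |

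**Step 3: a triggered rule.** The article does not define its trigger, so one was assumed: adjust for baseline only if a baseline t-test gives p < 0.05. Results from 20,000 simulated trials per scenario (180 per arm, r = 0.7, difference 0 or 0.25 SD):

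| Rule | Power | Type I error |
|---|---|---|
| Always adjust | 91.2% | 4.95% |
| Adjust if imbalanced, otherwise change score | 87.0% | 4.4% |
| Adjust if imbalanced, otherwise follow-up score | 68.0% | 3.8% |

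The triggered rule was conservative and lost power. The second row is the closest to what the article plans for CCTS.

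No gain was calculated for age, sex and education, or for the dichotomous outcomes, because the documents give nothing on how strongly these variables predict outcome.

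**The case against.** The other side has several good points.

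- A reader might infer from the logistic-regression sentence that baseline CCTS enters only if the arms look imbalanced. The text does not support this. That sentence follows the one on Fisher's test and concerns dichotomous outcomes. Baseline CCTS enters without any condition, through change from baseline and, with baseline as a visit, through the group-by-time model. For CCTS the relevant words are those on confounders in the mixed model.
- A reader might infer that the Table 3 p-values are the trigger. No passage says so. Table 3 describes the first 93 of 360 participants in a progress report, and the rule speaks of important non-comparability, not of significance. No formal schooling is 21.3% versus 8.7% with p = 0.235 for education (reproduced from counts of 10/25/12 and 4/29/13). This shows how little such a p-value says about a prognostic variable. It does not show a decision rule that failed.
- The large variance savings apply only against the visit-wise follow-up t-tests. Against the change score the gain is modest, and smallest where r is highest.
- The change score is unbiased under randomization, so the choice is one of efficiency. Fisher's test is planned whatever the balance, and nothing says that logistic regression would replace it.
- A covariate list may sit in an analysis plan that is not shown.

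All of this stands, and it limits the point. It does not remove it: the conditional rules are stated in the article, and a list kept elsewhere would not make a rule that waits for imbalance a good one.

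**Conclusion.** The point holds as one of efficiency and pre-specification. The article makes covariate adjustment depend on an undefined need (mixed model) or on observed imbalance (dichotomous outcomes), and no stated CCTS analysis uses baseline CCTS as a covariate.

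Against the planned change score, the loss is 5% to 25% of the variance for r from 0.9 to 0.5. Under the assumed 0.15-unit difference and SD 0.65 this is about 9, 6 and 2 percentage points of power at r = 0.6, 0.7 and 0.8. The visit-wise t-tests lose more: adjustment would cut their variance by r², or 25% to 81%. All these sizes rest on assumed r, SD, effect and full follow-up of 180 per arm, and the article itself expects attrition.

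A reader might also infer an inflated false-positive rate. The check does not show one: type I error under the assumed trigger was 3.8% to 4.4%. The harm is lost power and room for analyst discretion. The change should be made, but the planned analyses are not invalid without it.

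**What to change.** Make the primary CCTS analysis one mixed model that always adjusts for baseline CCTS, either as a covariate or through a common baseline mean across arms, and always for age, sex and education. Do the same for each continuous secondary outcome with its own baseline value. Replace the wording on adjustment where needed by this fixed list.

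For dichotomous outcomes, remove the imbalance trigger and run the covariate-adjusted analysis whatever the observed balance. State that an adjusted odds ratio is a conditional estimate and is not the same quantity as the unadjusted one. Baseline p-values should play no part in the choice of model.

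Cost: wording, and a sentence on interpreting the odds ratio. Table 1 schedules the neuropsychological battery and demographic data at baseline, and Table 3 already reports age, sex and education, so no new data are needed.
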